### Sample size

The sample size was estimated based on a comparison between the intervention group and the control group, represented by the improvement of the Fugl-Meyer Assessment of Upper Extremity (FMA-UE) as the primary outcome. In this study, a two-tailed test was chosen, *α* = 0.05. *μ*_*r*_ and *μ*_*c*_ represent the mean of FMA-LE scores after treatment in the intervention group (TCY-MIT + CRTs group) and the control group (CRTs group) respectively. *K* is the ratio of the sample size between the intervention group and the control group, so *K* = 1. According to the results of previous study [14], *μ*_*r*=_47.00, *μ*_*c*_=36.00, σ = 9, Δ = 3.6, *Z*_1 − *α*_= 1.96, and *Z*_1 − *β*_= 1.28. The calculated sample size of each group was approximately 32 individuals to achieve a power of 0.90 at a significance level of 0.05. After accounting for an anticipated dropout rate of 20%, the total number of patients required for this trial was 78, with 39 in each group. The formulas are as follows:
$$ {\displaystyle \begin{array}{c}{n}_r=\mathrm{K}{n}_c\\ {}{n}_c=\frac{{\left({Z}_{1-\alpha }+{Z}_{1-\beta}\right)}^2{\sigma}^2\left(1+\frac{1}{k}\right)}{{\left({\mu}_r-{\mu}_c-\Delta \right)}^2}\end{array}} $$

where *μ*_*r*_ is the mean of the intervention group, *μ*_*c*_ is the mean of the control group, *K* is the ratio of the sample size between the intervention group and the control group, Δ is the margin of superiority, and σ is the standard deviation.

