### Outcome measures and follow-up

Outcome measures will be performed by a certified, trained occupational therapist who is blinded to the group allocation of the participants. The assessments will be administered at baseline, after completion of the intervention (1, 2, and 3 weeks), and at the end of follow-up (2 months). Furthermore, resting-state fNIRS signal data collection will be a trained fNIRS technician.

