### Primary outcome measure

#### Motor function

The primary outcome measure is a change in score on the Fugl-Meyer Assessment of Upper Extremity (FMA-UE). The FMA-UE has been used to assess MIT-induced changes in upper extremity motor impairment in numerous RCTs [17, 18]. The acquired data are in the form of a 3-point ordinal scale (0 = cannot perform at all; 1 = can perform partially; 2 = can perform fully) that is calculated for each item [16]. The scale contains a total of 33 items, which are summed to provide the maximum score of 66. Assessors evaluated all participants immediately before therapy, after 3 weeks of therapy, and at the end of follow-up.

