### Statistical analysis

A sample size of 64 participants (32 per group) was determined to provide 90% power (*α* 0·05) to detect a mean FMA-UE difference of 11.0 (SD 9) points between the two treatment groups. The main analysis of this trial consists of a comparison of the outcomes after 3 weeks and at the end of follow-up (2 months). The statistician who is blinded to the group allocation of the participants will lock all data before statistical analysis. All data will be analysed with Social Sciences (SPSS) version 26.0 software (IBM Corporation, Armonk, USA) and GraphPad Prism version 9.0 software (GraphPad Software Inc., San Diego, USA). The baseline data and outcome analyses will be conducted on the full analysis set (FAS), using intent-to-treat (ITT) samples and completer samples. The per protocol set (PPS) will be used to analyse effective cases based on FAS. Furthermore, safety analysis will be performed on safety assessment set (SAS). Demographic data will be analysed using a two-sample *t*-test or Wilcoxon rank-sum test for continuous variables and the chi-squared test or Fisher’s exact test for categorical variables. For outcome, variables will be presented as the mean ± standard deviation ($$ \overline{x}\pm \mathrm{s} $$). Primary outcomes and secondary outcomes will be analysed using multivariable analysis of variance (ANOVA) for repeated measures, followed by Tukey's post hoc test. Statistical significance will be set at a *P value* less than 0.05.

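### Repeated-measures ANOVA followed by Tukey's test, in its classical pooled-error form, can mis-state the error of the 3-week and 2-month changes because the visits are unequally spaced

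*Protocol article*

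**What the plan says.** The protocol article, Statistical analysis, fixes one method for all outcomes: "Primary outcomes and secondary outcomes will be analysed using multivariable analysis of variance (ANOVA) for repeated measures, followed by Tukey" (the sentence ends by naming Tukey's post hoc test). The same section places the weight on two time points: "The main analysis of this trial consists of a comparison of the outcomes after 3 weeks and at the end of follow-up (2 months". The threshold follows: "Statistical significance will be set at a *P value* less than 0.05". The Sample size section adds "In this study, a two-tailed test was chosen".

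Under Primary outcome measure, the endpoint is a change: "The primary outcome measure is a change in score on the Fugl-Meyer Assessment of Upper Extremity (FMA-UE".

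The visit schedule appears in two forms. Outcome measures and follow-up says: "The assessments will be administered at baseline, after completion of the intervention (1, 2, and 3 weeks), and at the end of follow-up (2 months". For FMA-UE the text under Motor function lists three visits: "Assessors evaluated all participants immediately before therapy, after 3 weeks of therapy, and at the end of follow-up". On either schedule the last gap is the longest.

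The article names no error term, covariance structure or within-patient correlation, and does not say which means Tukey's test compares.

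**The concern.** Classical repeated-measures ANOVA with Tukey's test uses one error variance for every contrast. That is right only if the change between any two visits has the same variance (sphericity). When measurements further apart in time are less correlated, a 2-month change varies more than a 3-week change. A single averaged error is then too small for the longer contrast and, usually, too large for the shorter one.

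Those are the two contrasts on which the main analysis rests. At stake are a claim of lasting benefit at 2 months made more often by chance than the stated 5%, and a 3-week comparison with less power than its own variance would give. Correcting only the overall group-by-time F test would not repair post hoc contrasts that still use the pooled error.

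**Working it through.** **1. The plan's own figure.** Sample size section: n = (1.96 + 1.28)² × 9² × 2 / (47 − 36 − 3.6)² = 31.06, so 32 per group. With 20% dropout, 31.06 / 0.8 = 38.8, so 39 per group and 78 in total. The figure reproduces. It rests on one SD at one time and supplies no within-patient correlation.

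**2. Inputs.** From the article: 32 per group, two-sided 0.05, and three visits (weeks 0, 3, T) or five (weeks 0, 1, 2, 3, T). Assumed: T = 8.7 weeks if the 2 months run from baseline, or 3 + 8.7 = 11.7 if they run from the end of treatment; equal variance at each visit; and the correlation patterns below.

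**3. Formulas (large sample).**
- Variance of change between visits i and j: V = 2σ²(1 − correlation).
- The pooled error puts P, the mean of V over all visit pairs, in place of V.
- With r = √(P/V), the true level of a nominal 5% test is 2[1 − Φ(1.96 r)].
- If the contrast's own variance would give 90% power, pooled error gives Φ(3.24 − 1.96 r).

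**4. Worked example.** Three visits, T = 11.7, correlation 0.95 per week, σ² = 1.
- V(0,3) = 2(1 − 0.95³) = 0.285; V(0,11.7) = 2(1 − 0.95^11.7) = 0.902; V(3,11.7) = 2(1 − 0.95^8.7) = 0.720. Mean P = 0.636.
- 2 months: r = √(0.636/0.902) = 0.84; 1.96 r = 1.65; level 10.0%.
- 3 weeks: r = √(0.636/0.285) = 1.49; 1.96 r = 2.93; level 0.3%; power Φ(3.24 − 2.93) ≈ 62%.

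**5. Range, pooled error, no Tukey adjustment.** In the first four rows, values are for correlation 0.90 / 0.95 / 0.98 per week. Mixed means variance shares of 0.5 constant within patient, 0.4 decaying at 0.95 per week and 0.1 measurement error.

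| Visits, T | Correlation | 2-month level % | 3-week level % | 3-week power % |
|---|---|---|---|---|
| 3, 8.7 | decaying | 9.3 / 10.1 / 10.6 | 1.2 / 0.9 / 0.7 | 77 / 74 / 71 |
| 3, 11.7 | decaying | 9.1 / 10.0 / 10.6 | 0.6 / 0.3 / 0.2 | 70 / 62 / 57 |
| 5, 8.7 | decaying | 16.1 / 17.6 / 18.5 | 3.7 / 3.1 / 2.8 | 88 / 86 / 85 |
| 5, 11.7 | decaying | 16.4 / 18.0 / 19.0 | 2.4 / 1.7 / 1.3 | 84 / 80 / 78 |
| 3, 8.7 | mixed | 7.5 | 2.7 | 85 |
| 3, 11.7 | mixed | 7.8 | 1.8 | 81 |
| 5, 8.7 | mixed | 10.3 | 4.2 | 89 |
| 5, 11.7 | mixed | 11.2 | 3.4 | 87 |
| any | compound symmetry | 5.0 | 5.0 | 90 |

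Simulation under no treatment effect (32 per group, 20,000 trials per setting) agrees. It also gives 6–17% at 2 months for random slopes with five visits. With three visits (T = 11.7) the weakest slope gives 6.0% at 2 months and 3.8% at 3 weeks. If correlation falls by visit order rather than by elapsed time, five visits give 12–15% at 2 months and about 10% at 3 weeks, so the 3-week error changes direction.

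**6. With Tukey's critical value over visit means.** The studentized range divided by √2 replaces 1.96: about 2.37 for three visits and 2.75 for five. In the worked example, 2.37 × 0.84 = 1.99 gives about 4.6% at 2 months, and 2.37 × 1.49 = 3.54 gives 0.04% at 3 weeks. Over the decaying and mixed settings the 2-month level is about 2–7% and the 3-week level stays below 1%. Part of that 3-week loss is the multiplicity penalty, not the pooling.

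**7. With each contrast's own variance.** The simulated level is 4.6–5.5% at both time points in every setting.

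**The case against.** The strongest reply is that pooled error is inferred, not stated. The article calls the method multivariable, which may mean the multivariate approach. It is also a condensed account, and the error term and sphericity handling are commonly left to a full analysis plan. This stands in part. A missing sphericity correction is not itself a fault here, and no level can be asserted as the one the trial will have. But the article does fix a method. Its abbreviation list expands ANOVA itself with the same word, which suggests loose wording, and classical Tukey comparisons use one error variance.

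Second, Tukey's critical value can bring the 2-month level back near 5%. That is correct if Tukey runs over visit means, but there two errors offset each other and the 3-week contrast is left at about 1% or less. If Tukey compares only two groups it equals a t test and adjusts nothing.

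Third, if raw group means are compared at each visit with equal variances, simulation gives 4.3–5.4% throughout. This also stands, but that comparison does not test the change score named as primary.

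Fourth, the correlation is assumed. This stands fully, and is why compound symmetry is shown.

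**Conclusion.** The concern holds conditionally. The conditions are pooled error, contrasts of change from baseline, correlation that falls with time and no Tukey adjustment. The 2-month test of FMA-UE change then has a true level of about 6–11% with the three visits listed for that scale, or about 8–19% if five visits enter; a weak random slope with five visits can come as low as 6%. The 3-week test is usually conservative, mostly about 0.3–3% with three visits and 2–5% with five, with the most extreme settings slightly outside these ranges. A nominal 90% power falls to about 57–85% with three visits or 78–89% with five. Under compound symmetry both levels are 5%.

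A reader might infer that the 2-month change will be tested at 16–19%. The documents do not support that as a fact: it needs five visits, correlation decaying purely with elapsed time, and an unadjusted critical value. A reader might also infer that the errors always run in opposite directions. They do not, since the direction at 3 weeks depends on the covariance.

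**What to change.** In Statistical analysis, replace the ANOVA and Tukey step with between-group contrasts of change at 3 weeks and at 2 months from a repeated-measures model with unstructured within-patient covariance, so that each contrast uses its own variance. If the ANOVA is kept, state the Greenhouse-Geisser-corrected group-by-time test and use visit-specific error terms for the two contrasts.

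This changes one sentence and needs no new patients or data. The cost is a few degrees of freedom and possibly a wider interval at 2 months.

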## Discussion

Previous studies have investigated the effects of actual TCY on the recovery of upper extremity motor dysfunction in poststroke patients [8, 9]. Scholars have found that kinesthetic motor imagination and visual motion imagination can both mobilize cortical reorganization and neuronal excitability, which could cause structural and functional remodelling, thereby promoting behavioural recovery [21–23]. Hence, we will combine MIT, converting actual TCY to kinesthetic motor imagination that fits poststroke patients with hemiplegia who cannot move or have severely impaired movement in their affected upper limb. With the development of neuroimaging, many studies use objective data to evaluate and predict the prognosis of poststroke patients with damaged brain function [24, 25]. We chose cerebral cortex blood oxygen changes to assess neural activity and regulation of the cerebral cortex after this combination therapy because compared with other neuroimaging activity collection methods, fNIRS is more convenient and has a wider range of applications [26, 27]. All of the clinical procedures will be performed in the hospital, and this treatment will be done with professional guidance. Therefore, the use of TCY-MIT combined with CRT to treat poststroke patients’ upper extremity motor dysfunction is available and safe under this setting. Our hypothesis is that UE-MF, manual dexterity, finger muscle strength, and activities of daily living will be better improved after TCY-MIT combined with CRTs compared with CRTs alone. More effective brain network connections between damaged brain areas or between normal brain areas and damaged brain areas were observed in the TCY-MIT combined with CRTs group, which is based on fNIRS resting-state collection. If the results are as anticipated, this will promote the understanding of the neurological activity of TCY-MIT in poststroke patients. In addition, combination therapy could be widely adopted in poststroke communities with dyskinesia to reduce the global burden of stroke.

Our study has several strengths. (1) the design and report of the trial protocol strictly follow the SPIRIT statement, and this study will adhere to CONSORT 2010. (2) The TCY exercise is a household name, group training program. It is easy to conduct TCY-MIT in the stroke population and to improve the participants’ compliance. (3) Few studies have examined neural activity during TCY-MIT. We will capture cerebral cortex blood oxygen changes during neural activities to reveal the potential mechanisms of TCY-MIT combined with CRTs via fNIRS-based resting-state brain network analysis. We hypothesized that compared with the control group, participants in the intervention group will show increased brain functional connectivity and that the *r* value is related to the primary outcome. The fNIRS technician (blinded to the group allocation of the participants) will be assigned to take charge of fNIRS-based resting-state data collection and analysis. (4) In this trial, we are not only focusing on the recovery of motor function after the intervention, but we are also using the MBI score as an outcome measure to assess ADL in poststroke patients after completion of the interventions (3 weeks) and at the 6-month postintervention follow-up (2 months).

However, there are a few limitations. First, the intervention time for stroke patients is only 3 weeks due to the duration limit of hospitalization that is set for the patients. Second, this is a single-centre study. A multicentre, larger sample size is required to prove our objectives. Third, it is difficult to objectively monitor whether the participants are engaging in TCY-MIT rather than other mental activities. Fourth, the study does not use fNIRS to perform analysis of cortical activation with tasks.

In summary, the results of the study will be beneficial to optimize rehabilitation training methods and provide new therapeutic ideas for stroke rehabilitation. Our team will further explore the individualized rehabilitation program of TCY-MIT in future work.

## Trial status

Recruitment for this trial is currently ongoing. And the study will be completed in June 2022.

## Data Availability

The datasets used and/or analysed after completing the current study will be available from the corresponding author by reasonable requests.

## Abbreviations

ADL: Activities of daily living
ANOVA: Multivariable analysis of variance
BBT: Box and Block Test
BI: Blinding index
CRTs: Conventional rehabilitation therapies
CRFs: Case report forms
CT: Computed tomography
FMA-UE: Fugl-Meyer assessment of Upper Extremity
KVIQ-20: Kinesthetic and Visual Imagery Questionnaire-20
FAS: Full analysis set
fNIRS: Functional near-infrared spectroscopy
ITT: Intent-to-treat
MIT: Motor imagery training
MBI: Modified Barthel index
MST: Muscle strength test
MRI: Magnetic resonance imaging
MMSE: Mini-Mental State Examination
OT: Occupational therapy
PPS: Per protocol set
PT: Physical therapy
RCTs: Randomized controlled trials
r: Pearson’s correlation coefficient
SPIRIT: Standard Protocol Items: Recommendations for Interventional Trials
SPSS: Statistical Package for the Social Sciences
SAS: Safety assessment set
TCY-MIT: Tai Chi Yunshou motor imagery training
UE-MF: Upper extremity motor function
